**Table 1: Doses of CQ & PQ by body weight**

| **Weight (kg)** | **Primaquine base, 7.5 mg**  **Number of tablets/day**  **(Total = 10 days)** |
| --- | --- |
| **5-6** | 1/4 |
| **7-10** | 1/2 |
| **11-14** | 3/4 |
| **15-18** | 1 |
| **19-21** | 1+1/4 |
| **22-25** | 1+1/2 |
| **26-29** | 1+3/4 |
| **30-33** | 2 |
| **34-36** | 2+1/4 |
| **37-40** | 2+1/2 |
| **41-44** | 2+3/4 |
| **45-48** | 3 |
| **49-51** | 3+1/4 |
| **52-55** | 3+1/2 |
| **56-59** | 3+3/4 |
| **60+** | 4 |

| **Weight (kg)** | **Chloroquine base, 150mg**  **Number of tablets** | | |
| --- | --- | --- | --- |
| **Day0** | **Day 1** | **Day 2** |
| **5-6** | 1/2 | 1/4 | 1/4 |
| **7-10** | 1/2 | 1/2 | 1/2 |
| **11-14** | 1 | 1 | ½ |
| **15-18** | 1 | 1 | 1 |
| **19-24** | 1.5 | 1.5 | 1 |
| **25-35** | 2.5 | 2.5 | 1 |
| **36-50** | 3 | 3 | 2 |
| **50+** | 4 | 4 | 2 |

**28-day follow up**

During the 10-day treatment, patients will be examined daily, then weekly at day 14, 21 and 28, following detailed procedures in Table 2. Patients will be visited at home by the study team, and if the patient is absent every effort will be done to trace him before the next scheduled visit. Clinical signs and symptoms, especially adverse events (AE) will be assessed at each scheduled visit; early signs of haemolytic anaemia will be systematically checked (colour of urine and conjunctives). All signs and symptoms will be recorded on a standardised pre-coded questionnaire (Annex7). Blood samples will be collected according to the predefined schedule in Table 2. In case of fever, or any new symptoms appearing between the scheduled visits, patients will be asked to consult either their hamlet health worker (HHW) or the CHC for a clinical and biological assessment. In case of recurrent *P.vivax* parasitemia during the 28-day follow-up, a blood sample will be taken by finger prick (100µl with a heparinised µcapillary) for later dosage chloroquine blood level measurement. Any *P.vivax* treatment failure (early or late clinical failure), or a new infection with *P.falciparum,* will be treated with Arterakine for 3 days (Artesunate+piperaquine) according to the national guidelines. In this case, the patient will still remain in the follow-up (28-day and 2-year monthly follow-up).

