### Rescue treatment

- With any sign of severe malaria, the patient should be administered parenteral antimalaria treatment with either quinine or artesunate (IV) following national guidelines;
- If a patient meets one of the criteria for therapeutic failure (ETF, LTF), he/she will receive Arterakin for 3 days following the national guideline. However, this patient will remain in the 2-year monthly follow-up, and thus should be re-assessed clinically and biologically at Day 28 (following D28 procedures mentioned in Annex7), and then enter the monthly follow-up.
- If the patient is re-infected with *P.falciparum* (mono- or mixed infection) he/she will receive the rescue treatment with Arterakin for 3 days following the national guideline.

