### Study endpoints

- Primary Endpoint

There will be two primary end points for determining the efficacy of the *P. vivax* national treatment guidelines:

- Treatment Failure (TF) at day 28 (see below);
- Incidence of *P. vivax* (recurrent) infection after day 28 during the 2-year follow up;

The TF is defined as the sum of early* and late** treatment failures.

- * Early Treatment Failure (ETF) (one of the following)

(i) Development of danger signs on Day 0, Day 1, Day 2 or Day 3, in the presence of parasitaemia;

(ii) Parasite density on Day 2 > Day 0 count, irrespective of axillary temperature,

(iii) Presence of parasitaemia on Day 3 with fever (axillary temperature ≥ 37.5°C),

1. Parasitaemia on Day 3 ≥ 25 % of count on Day 0.

- ** Late treatment failure (LTF)
- LTF is divided in late clinical and late parasitological failure.

Late Clinical Failure (LCF):

(i) Development of danger signs on any day after Day 3 in the presence of parasitaemia, without previously meeting any of the criteria of Early Treatment Failure;

(ii) Presence of parasitaemia and fever on any day after Day 3, without having previously meet the criteria of ETF.

Late Parasitological Failure (LPF):

Presence of parasitaemia on any day from day 7 onwards and axillary temperature <37.5 ºC, without previously meeting any of the criteria of Early Treatment Failure or Late Clinical

Failure.

*****The adequate clinical and parasitological response (ACPR)** is 1-TF. It is defined as absence of parasitaemia at the end of the follow up period (day 28), irrespective of axillary temperature without previously meeting any of the criteria of early and late treatment failure. In the adjusted estimates, patients with late asexual parasite reappearance (with or without fever) will be considered ACPR if the PCR analysis shows a new infection rather than a recrudescence.

- Secondary Endpoints

The secondary endpoints will be:

- Asexual parasite clearance time (PCT): Asexual parasite clearance time will be defined as the time (in days) from the day of randomization to 2 consecutive negative blood slides (collected at different days). The time to the event will be taken as the time to the first negative slide.
- Gametocytaemia (prevalence and density) at day 7, 14, 21, 28 after treatment;
- Hemoglobine changes between day 0 and day 14 and 28.

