### Sample size calculation

Two different sample sizes were calculated: one for the estimation of *P.vivax* failure rate for chloroquine (28-day follow-up) and for Primaquine (2-year follow-up) in a cohort of *P.vivax* patients initially treated with the current radical cure regimen, and the second for the population survey on *P.vivax* prevalence (in a random sample of the study population).

- ***P.vivax population survey***

A total2,100 individuals at risk of malaria were estimated in the 4 study communes (census February 2009). According to the provincial malaria station (PMS) data on surveys carried out in April-May, the overall parasite rate was around 16% (ranging from 5 to 39% across hamlets) and the prevalence of *P.vivax* at 9%. In order to detect a minimal prevalence of 9% with 3% precision and at 5% significance level, a total of 300 individuals is needed for the survey (“CSample” command/EpiInfo6). After “finite population correction” and adding 10% security margin, a final sample size of 300 individuals would be sufficient. Since there are a total of about 370 households and in order to simplify sampling procedures, one individual in each house visited for the screening will be randomly selected to participate in the survey. This will be done by randomly choosing from the census file. The selected individual will be asked oral informed consent before starting in-depth interview.

- ***P.vivax cohort***

Between 2003 and 2007, *P. vivax* late parasitological failure to CQ was monitored in several Central Vietnam provinces and ranged from 0% to 5.7% (13). Therefore, to detect a failure rate as low as 5% with a 3% precision at 5% significance level, a minimum of 185 individuals are needed (“CSample” command/EpiInfo6). Assuming a maximum drop out rate of 10% during the first 28 days, a total of 204 cases will be necessary. For the estimation of a similar PQ failure rate after 2 years of follow-up, a total of 230 patients should be included with a maximum of 20% drop out during the 2-year follow-up.

By including 250 vivax patients in the cohort, and assuming a maximum drop out rate of 20% during the 2-year follow-up, we can expect to get a final database of 200 patients with a complete follow-up (i.e. 31 successive sampling results) for the modelling of *P.vivax* new infections/relapses.

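### Sections 3.2.4 and 3.3.3 give opposite instructions on rescue for late parasitological failure, and if such an infection persists past Day 28 it could count in both primary endpoints

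*Protocol*

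**What the plan says.** Four places in the protocol bear on the point.

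- **Section 3.2.4 (Rescue treatment):** "If a patient meets one of the criteria for therapeutic failure (ETF, LTF), he/she will receive Arterakin for 3 days". Nothing here restricts late failure to its clinical form. The patient stays in the 2-year follow-up.
- **Section 3.2.5 (Study endpoints):** "LTF is divided in late clinical and late parasitological failure". The parasitological class is defined as "Presence of parasitaemia on any day from day 7 onwards and axillary temperature <37.5 ºC", in patients who have not already met an early or late clinical failure criterion. The first primary endpoint, treatment failure at Day 28, is the sum of early and late failures and so includes LPF. The second counts *P. vivax* ("recurrent) infection after day 28 during the 2-year follow up").
- **Section 3.3.3 (28-day follow up):** Arterakine is given for "treatment failure (early or late clinical failure), or a new infection with" *P. falciparum*. For recurrent *P. vivax* parasitaemia before Day 28, the section otherwise asks only for a blood sample to measure the chloroquine level.
- **Section 3.3.3 (2-year monthly follow-up):** recurrent *P. vivax* parasitaemia found in this phase is treated with chloroquine alone, a different drug from the Day-28 rescue.

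**The concern.** A patient with a positive slide and no fever between Day 7 and Day 28 is rescued under one section and is absent from the rescue list in the other. The protocol is built to find such patients, because Table 2 schedules slides on Days 7, 14, 21 and 28 whether or not there is fever. LPF is also the failure type whose observed range supports the 5% planning rate in section 3.2.6.

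Two things are at stake. First, patients with the same finding could be managed differently, depending on which section the team has in hand. Second, an infection left unrescued could still be present at the first monthly visit. The second primary endpoint, as worded, neither requires a negative slide first nor excludes patients who have already failed by Day 28.

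**Working it through.** **1. The rescue lists side by side**

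| Failure class (section 3.2.5) | Rescue under 3.2.4 | Rescue under 3.3.3, 28-day follow up |
| --- | --- | --- |
| Early treatment failure, including criteria based only on parasite counts | Yes | Yes |
| Late clinical failure | Yes | Yes |
| Late parasitological failure | Yes, as part of late failure | Not listed |

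The lists differ in one row only. The descriptions of Days 1 to 9, Days 14 and 28, Day 21 and unscheduled visits contain no treatment rule for a failure, so they do not decide between the two.

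**2. The plan's own figure**

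Section 3.2.6 plans for a 5% failure rate with 3% precision at the 5% level and states 185 patients.

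- n0 = 1.96² × 0.05 × 0.95 / 0.03² = 202.7
- With a finite population correction for the 2,100 inhabitants: 202.7 / (1 + 202.7/2,100) = 184.9, that is, 185.

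The correction is my assumption for the cohort calculation, but it reproduces the stated number. The sample size is not in dispute. It shows only that the 5% rate, drawn from LPF monitoring data, is the design rate.

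**3. Patients under conflicting instructions**

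Inputs from section 3.2.6: LPF 0% to 5.7%, and 250 patients to be included.

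- Lower end: 0 × 250 = 0
- Planning rate: 0.05 × 250 = 12.5
- Upper end: 0.057 × 250 = 14.25, about 14

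**4. Route to a double count**

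All of the following must happen:

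1. The patient meets LPF, and so is a Day-28 treatment failure.
2. Staff follow section 3.3.3 rather than 3.2.4 and give no rescue.
3. The patient stays afebrile while parasitaemic through Day 28. Parasitaemia with fever after Day 3 is late clinical failure, which both sections rescue.
4. Parasitaemia is still present at a visit after Day 28 and is recorded as a recurrence.

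Let *f* be the share of LPF patients who pass steps 2 to 4. The number counted twice is *f* × (number with LPF). The documents give no value for *f*. At the top of the LPF range:

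- *f* = 0: 0 patients
- *f* = 0.5: 0.5 × 14.25 = 7.1 patients
- *f* = 1: 14.25 patients

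At 0% LPF the result is 0 for every *f*. The total of Day-28 failures is the same under either section, because an LPF patient is already a failure. Only the second primary endpoint would be affected.

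**The case against.** The best defence is that the parenthesis in section 3.3.3 is loose shorthand. The sentence opens by referring to any *P. vivax* treatment failure, section 3.2.5 counts LPF as one, and section 3.2.4 is the section devoted to rescue. Section 3.3.3 never says that LPF goes untreated. This is a possible reading, but the parenthesis specifies which failures are meant and omits a class that section 3.2.5 names separately. Field staff working from section 3.3.3 have no reason to add it.

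A second defence is that uninterrupted parasitaemia is not recurrent in the ordinary sense, and that a counting rule could sit in an analysis plan. That has weight: the missing counting rule would not be a finding on its own. But an analysis plan cannot tell staff whether to treat an afebrile positive patient, and the protocol gives two answers. Genotyping of recurrences (section 3.4) does not settle the count either. The only PCR adjustment stated among the endpoints concerns the adequate clinical and parasitological response, not the second primary endpoint.

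Two stronger readings are tempting, and the documents support neither.

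- *That section 3.3.3 rescues clinical failures only.* It also covers early failures, some of which are defined purely by parasite counts. The gap is LPF alone.
- *That the double count would roughly double the 2-year failure rate, from 5% to about 10%.* This takes LPF near the top of its range and assumes that every case persists. It also adds LPF to a planned primaquine failure rate, whereas the second primary endpoint is the incidence of recurrent infection, with no stated exclusion of new infections. The protocol does not show these to be the same quantity.

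**Conclusion.** The contradiction stands on the text alone: section 3.2.4 read with section 3.2.5 includes LPF in rescue, and the 28-day part of section 3.3.3 leaves it out. It concerns a component of the first primary endpoint and affects 0 to about 14 of 250 patients, given the cited LPF range and full enrolment.

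The double count is a conditional consequence. It requires that section 3.3.3 be the text followed, that the patient remain afebrile and parasitaemic through Day 28, and that the later positive slide be scored as a recurrence. Its size cannot be fixed from the documents. I take no position on which rescue instruction is right.

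**What to change.** - Reconcile sections 3.2.4, 3.2.5 and 3.3.3 so that a single list of failure classes governs rescue and every section refers to it. The clinical lead decides what the list contains.
- Add one sentence to the second primary endpoint: parasitaemia continuing from a Day-28 failure without an intervening negative slide is not a new event.

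The cost is wording in the rescue and follow-up sections plus one counting rule. The slides already scheduled up to Day 28 and at each monthly visit supply the data for that rule, so no additional patients, visits or samples are needed.

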**Table 2. Patients’ follow-up schedule during the first 28 days**

|  | **D0** | **D1** | **D2** | **D3** | **D4** | **D5** | **D6** | **D7** | **D8** | **D9** | **D14** | **D21** | **D28** | **Dx** | **M*** | **Mx** |
| --- | --- | --- | --- | --- | --- | --- | --- | --- | --- | --- | --- | --- | --- | --- | --- | --- |
| **PROCEDURES** |  |  |  |  |  |  |  |  |  |  |  |  |  |  |  |  |
| Clinical examination | **X** | **X** | **X** | **X** | **X** | **X** | **X** | **X** | **X** | **X** | **X** | **X** | **X** | **X** | **X** | **X** |
| Assess adverse event | **X** | **X** | **X** | **X** | **X** | **X** | **X** | **X** | **X** | **X** | **X** | **X** | **X** | **X** |  |  |
| Body temperature | **X** | **X** | **X** | **X** | **X** | **X** | **X** | **X** | **X** | **X** | **X** | **X** | **X** | **X** | **X** | **X** |
| Thick+thin film | **X** | **X** | **X** | **X** |  |  |  | **X** |  |  | **X** | **X** | **X** | **X** | **X** | **X** |
| Filter paper 2 spots  (ELISA & PCR) | **X** |  | **X** | **X** |  |  |  | **X** |  |  | **X** | **X** | **X** | **X** | **X** | **X** |
| Hemoglobin | **X** |  |  |  |  |  |  |  |  |  | **X** |  | **X** |  |  |  |
| Filter paper CQ  (100µl capillary) | **X** |  |  |  |  |  |  | **X** |  |  |  |  | **X** | **X** |  |  |
| Direct observation of treatment | **X** | **X** | **X** | **X** | **X** | **X** | **X** | **X** | **X** | **X** |  |  |  |  |  |  |

**Dx**: Any other day if the patient feels febrile or unwell

**M***: monthly visits by HHW from 2nd to 24th month

**Mx:** unscheduled monthly visit if patient feels sick

**Day 0: Enrollement/ administration of the study medication**

Demographic Data and Medical History

Demographic data and a general history of past and present illnesses will be recorded onto to the pre-coded standardised form for the 28-day follow-up.

Informed consent

After an in-depth interview, with one physician of the study or with another qualified person, the patient (or the parent/legal guardian) will be asked to document his/her consent by signing an informed consent form; if the patient is minor of age/not emancipated, the consent must be given by a parent or legal guardian according to national law. However, in this case, the investigator is responsible to check that the patient is also freely willing to take part in the study. The signed informed consent (or thumb-printed whenever the patient or the parents/guardians are illiterate) must be obtained before any tests or evaluations related to the study are carried out. However, a thick blood film or a rapid diagnostic test before the informed consent can be done as this can be considered a normal procedure for the management of patients suspected having clinical malaria.

Physical and Clinical Examination

A general physical examination will be performed.

A clinical examination will be performed: symptoms and axillary temperature (mercury thermometer).

Vital Signs and Weight

Vital signs (respiratory rate and pulse) and weight will also be measured (see details in patient’s form for 28-day follow-up).

Blood slides:

Thick and thin films will be prepared following the SOP (standard operating procedures) for laboratory. Blood slides will be examined for the confirmation of *P. vivax* mono-infection and parasite density.

Blood slides will be independently read by 2 qualified microscopists, data entered in separate files. Further details are described and explained in the SOP (SOP: Quality control (QC) guidelines for the laboratories participating in the study).

Parasite density will be calculated by counting the number of asexual parasites per 200 leukocytes in the thick blood film, based on an assumed WBC of 8,000 /µl by light microscopy at 1000xmagnification. The parasite density per microlitre will be calculated using the following formula:

Parasite density / µl = Number of parasites counted x 8,000

Number of leukocytes counted

PCR/ELISA

A blood sample (2 spots of at least 1.5cm diameter) will be collected on filter paper (Whatmann grade 3) at day 0 before treatment and every time a blood slide is done. Samples from patients classified as late treatment failure will be subsequently used for parasite genotyping. ELISA test for detecting CSP protein will be done on all blood samples at of the 28-day and monthly follow-up. Antibodies against the CSP are specifically produced during a new *P.vivax* infection (but not during relapses).

Haemoglobin (Hb)

Haemoglobin will be measured directly by using the HemoCue method following the SOP for laboratory. Briefly a drop of capillary blood is taken with a microcuvette which is then put in the reader. After 10” the Hb level appears on the screen. The result is directly recorded on the patient’s form.

Blood sample for CQ blood level measurement

100µl of capillary blood is taken with a microcapillary and poured onto a filter paper (Whatman grade 3).

Administration of the Study Drugs by a study doctor or nurse

CQ and PQ according to the patient’s body weight (Table 1).

Adverse Events Report

All adverse events will be recorded.

Concomitant Medications

Any medications taken by the study subject will be recorded.

**Day 1 -9: *Treatment Period***

Physical and Clinical Examination

A general physical examination and a clinical examination will be performed: symptoms, axillary temperature (mercury thermometer). An in-depth interview on potential risk factors (last month’s activities and malaria prevention measures taken) will be administered as soon as the patient feels well to answer questions. All data will be recorded on the patient’s follow-up (Annex7b)

Vital Signs

Vital signs (respiratory rate and pulse) will be measured.

Blood Slide at day 1-2-3 and 7

A thick and thin blood smear will be obtained to verify the presence and to determine the density of asexual and sexual stages of *P*. *vivax*.

PCR/ELISA

A blood sample will be collected any time a blood slide is done (Whatmann grade 3) for later genotyping.

CQ blood level at day7

100µl of capillary blood will be taken and poured on a filter paper (Whatmann grade 3) for later CQ blood level measurement in case of a *P.vivax* recurrence during the 28-day follow-up.

Concomitant Pharmacological Treatments

Concomitant medications being taken by the patients will be recorded.

Adverse Events Report

All adverse events will be recorded.

Administration of the Study Drugs by a study doctor or nurse

CQ at day 1 and 2. PQ from day 1 until day 9.

**Day 14 and 28: *Follow up***

Physical and Clinical Examination

A general physical examination and a clinical examination will be performed: symptoms, axillary temperature (electronic thermometer).

Vital Signs

Vital signs (respiratory rate and pulse) will be measured.

Blood Slide

A thick and thin blood smear will be obtained to verify the presence and to determine the density of asexual and sexual stages of *P*. *vivax*.

PCR/ELISA

A blood sample will be collected any time a blood slide is done (Whatmann grade 3) for later genotyping.

Haemoglobin

1 blood sample will be taken for direct Hb measurement (HemoCue).

Concomitant Pharmacological Treatments

Concomitant medications being taken by the patients will be recorded.

Adverse Events Report

All adverse events will be recorded.

**Day 21: *Follow up***

As for day 14, without Hb

**Unscheduled visit until day 28**

As Day 21. In case of a *P.vivax* recurrent infection, a blood sample for later CQ blood level measurement will be taken (100µl capillary blood onto a filter paper)

***2-year monthly follow-up***

After completion of the 28-day follow up, patients will be visited monthly at home by a health staff from the study team. Each patient will be interviewed on malaria signs/treatment since the last visit, examined clinically (body temperature) and a blood sample (slide +filter paper) will be taken. All information will be recorded on a pre-coded standardised questionnaire (monthly follow-up form). In case a patient presents with a recurrent *P.vivax* parasitemia s/he will be treated with CQ alone for 3 days. In case of persistent *P.vivax* gametocytemia, the patient can be treated with a single dose of Primaquine (0.75mg/kg). *P.falciparum* mono- or mixed infections will be treated with Arterakine according to the national guidelines. Blood slides will be stained and read within 48h at Tra leng CHC and stored as well as filter papers in a dry, cool place.

If the patient is not available on the day of the scheduled visit, it is the responsibility of the HHW to trace him/her back before the next scheduled visit. If a patient cannot be traced for a whole month, the HHW has to report it (together with the reason of absence) on the monthly follow-up form. Cohort patients will be asked to consult their HHW (or the CHC) for any symptom appearing between the monthly scheduled visits, for clinical and biological examination by the study team.

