### Cohort recruitment

Vivax infected patients will be recruited during the initial screening/survey and/or during one year of the passive case detection (PCD) continued in each study village during the whole cohort follow-up.

Initially, the recruitment period was foreseen from April 2009 to April 2010. Since only 117 *P.vivax* patients could be recruited by February 2010, it was decided to extend the recruitment until December 2010 in order to reach the target number of 250 patients included.

*Inclusion criteria*

- Age ≥ 3years
- *P.vivax* mono-infection (asexual stages);
- Resident in the study villages;
- Written informed consent (parent/guardian for minors);

*Exclusion criteria*

- General danger signs with severe or complicated malaria according to WHO definitions (Annex B to this protocol);
- Pregnancy (rapid test positive or pregnancy clinically confirmed) or breastfeeding;
- Known G6PD deficiency (or history of “black urine” after previous primaquine treatment), or any history of side effects to the study drug;
- Documented radical cure with Primaquine (10 days at 0.5mg/kg) within one month prior to inclusion;
- Underlying chronic diseases (TB, lupus, diabetes, rheumatoid arthritis, etc);
- Concomitant infectious disease requiring antibiotic treatment;
- Severe malnutrition;
- Patients with neuro-psychiatric disorders or previous history (epilepsy, dementia, ..)

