### Patient discontinuation or protocol violation

Cohort patients meeting any of the following criteria will be classified as **withdrawn**

- **Withdrawal of consent:**

Any patient may withdraw consent at any time, without prejudice for further follow-up or treatment in the study site.

- **Failure to complete the treatment due to either:**
- Failure to attend the scheduled visits during the 10-day treatment;
- Serious adverse events necessitating termination of the treatment before the full course (10 days) of the treatment is completed;

A patient who vomits twice the study medications will be withdrawn from the study and given the rescue treatment.

A patient can be discontinued from the study if the investigator decides that a patient should be withdrawn for safety reasons due to serious adverse events (signs of hemolytic anemia (yellow conjonctives/dark urine) or Grade 3 to 4 of the WHO classification for adverse events). In this case, information concerning the adverse event and symptomatic treatment given must be recorded on the patient follow-up form (Annex 7).

- **Voluntary protocol violation (28-day follow-up)**

Self- or third party administration of antimalarial (or antibiotics with antimalarial activity such as tetracycline, amoxicilline).

- **Involuntary protocol violation (during the 28-day follow-up)**
- Occurrence of concomitant disease that would interfere with a clear classification of the treatment outcome;
- Detection of another malaria species during the follow-up;
- Erroneous inclusion of a patient who do not meet the inclusion criteria;
- Misclassification of a patient due to a laboratory error (parasitaemia) leading to the administration of the rescue treatment;

**Patients who are withdrawn will be followed up until day 28 and continue the 2-year monthly follow-up.** However, no treatment outcome will be assigned to these patients during the 28-day follow-up. The reason for discontinuation or protocol violation will always be recorded on the follow-up forms (Annex 7 or Annex 8, accordingly).

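### Primaquine in the monthly phase is not reconciled with the entry exclusions or earlier safety withdrawals, and Table 2 schedules no adverse event assessment there although antimalarials are given

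*Protocol*

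**What the plan says.** Four places in the Protocol bear on this.

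- **2-year monthly follow-up (section 3.3.3).** Recurrent P. vivax parasitaemia is treated with chloroquine alone, and P. falciparum or mixed infection with Arterakine. Where P. vivax gametocytaemia persists, "the patient can be treated with a single dose of Primaquine (0.75mg/kg").
- **Patient discontinuation or protocol violation (section 3.2.3).** A serious adverse event that ends the 10-day course early is a ground for withdrawal. The investigator may also decide that a patient should be "withdrawn for safety reasons due to serious adverse events (signs of hemolytic anemia (yellow conjonctives/dark urine"), among other grounds. The section then states, without exception: "Patients who are withdrawn will be followed up until day 28 and continue the 2-year monthly follow-up".
- **Cohort recruitment, exclusion criteria (section 3.2.1).** The list includes "Pregnancy (rapid test positive or pregnancy clinically confirmed) or breastfeeding". It also includes known G6PD deficiency or black urine after earlier primaquine, "or any history of side effects to the study drug".
- **Table 2.** The row "Assess adverse event" is marked on every scheduled day up to D28 and for Dx. It is blank for M*, defined as "monthly visits by HHW from 2nd to 24th month", and for Mx, the unscheduled visit in that phase.

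**The concern.** A patient whose primaquine course was stopped for haemolytic signs stays under study care for two years. So does a woman who becomes pregnant after enrolment. If either has persistent gametocytaemia at a monthly visit, the only text that governs the visit permits primaquine and does not direct staff to the earlier event or to current pregnancy status. The same person presenting for enrolment that day would be refused entry to the cohort. Staff who follow the monthly section as written could therefore re-expose a patient whom the study already knows to have reacted to the drug.

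The second matter is what is recorded afterwards. The study directs antimalarial treatment for about two years but schedules structured adverse event assessment for 28 days only. Harm after monthly-phase treatment would come to light only through general examination or the patient's own report, so any safety statement about that phase would rest on incomplete ascertainment.

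**Working it through.** No arithmetic beyond counting columns applies, and the plan gives no figure to reproduce. The check sets the sections side by side.

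**Step 1: can a patient with haemolysis reach the monthly phase?** Yes. Signs of haemolytic anaemia are named as a safety ground for withdrawal, and withdrawn patients continue into the monthly follow-up with no exception by reason of withdrawal. The entry exclusion covers only known G6PD deficiency, and Table 2 has no G6PD row. A reaction during the 10-day course is therefore one way in which an unrecognised deficiency could first show itself.

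**Step 2: can a pregnant or breastfeeding patient be in the monthly phase?** Yes. Pregnancy and breastfeeding are assessed for entry. Table 2 has no pregnancy-test row, and a later pregnancy is not among the listed grounds for withdrawal.

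**Step 3: does the monthly section restrict primaquine for them?** It sets one condition, persistent P. vivax gametocytaemia, and uses permissive wording. It states no exception for earlier haemolysis, side effects, pregnancy or breastfeeding. The Arterakine sentence in the same paragraph refers to the national guidelines; the primaquine sentence does not.

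**Step 4: is the earlier information at hand?** The section on discontinuation sends the details of a safety event to the 28-day form (Annex 7). It says that the reason for discontinuation goes on Annex 7 or Annex 8, as applicable. It does not say that a reason recorded during the first 28 days is carried forward to the monthly visit.

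**Step 5: what does Table 2 schedule?**

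| Row | D0 to D9 | D14, D21, D28 | Dx | M* | Mx |
|---|---|---|---|---|---|
| Clinical examination | 10 of 10 | 3 of 3 | yes | yes | yes |
| Adverse event assessment | 10 of 10 | 3 of 3 | yes | blank | blank |

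- Scheduled days with adverse event assessment up to day 28: 10 + 3 = 13, plus Dx.
- Monthly visits, months 2 to 24: 24 − 2 + 1 = 23, of which 0 carry adverse event assessment.

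Dx and Mx are both unscheduled visits by a patient who feels unwell, yet only Dx has the mark. The systematic check of urine and conjunctival colour is likewise described only in the 28-day section.

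**Result.** Steps 1 to 3 show a path, open under the text, from safety withdrawal or new pregnancy to primaquine in the monthly phase. Step 4 shows no stated safeguard that closes it. Step 5 shows that structured adverse event assessment ends while study-directed treatment continues.

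**The case against.** The strongest reply is that the exclusion criteria govern entry to the cohort and set no rule on who may receive primaquine. That is correct. The section on screening and survey even offers non-eligible P. vivax patients treatment under the national guidelines, with chloroquine and primaquine named. A reader might infer that the protocol forbids primaquine in one place and orders it for the same patient in another. The text does not support this: no section directs primaquine for a pregnant patient or one with earlier haemolysis. The conflict arises from silence.

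A reader might also infer that any cohort patient may be given the dose. That is too broad, because it is tied to persistent gametocytaemia and left to discretion. Withdrawal for haemolytic signs is itself partly a matter of the investigator's judgement. Discretion lowers the likelihood of re-exposure, but the text gives whoever exercises it no pointer to the earlier event.

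On data collection, the reply is that Table 2 is titled for the first 28 days, the monthly form is not among the documents shown, monthly visits include an examination and an interview on malaria signs and treatment, and patients are asked to come forward with any symptom between visits. This is real mitigation. It rules out the inference that later harms could not be reported at all. It does not explain the blanks: Table 2 does carry columns for the monthly phase and marks other procedures in them.

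Haemoglobin is also unmarked in the monthly phase, but this agrees with the stated endpoint, "Hemoglobine changes between day 0 and day 14 and 28", and is no defect.

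**Conclusion.** The point holds as an unreconciled gap. The sections on recruitment, discontinuation and monthly follow-up do not settle whether the entry exclusions, or an earlier withdrawal for safety, apply to primaquine given in the monthly phase. Table 2 schedules no adverse event assessment at the 23 monthly visits or at unscheduled visits in that phase, although three antimalarial treatments may be given there.

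The size cannot be stated as a number of patients. It would need the frequency of haemolytic reactions or new pregnancies, of persistent gametocytaemia among those patients, and of decisions to dose; the documents give none of these, and the group may be small. A reader might be tempted to gauge the problem by multiplying the cohort size by the number of monthly visits, or by comparing the single dose with the daily dose of the initial course. Neither measures it: the first counts visits at which nothing was given, and the second says nothing about how many patients are at risk.

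The conclusion assumes that staff follow the monthly section and Table 2 as written, and that no form outside the documents already carries the missing items. Because the matter is patient safety and the remedy is cheap, it should be resolved. Neither primary endpoint is affected.

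**What to change.** 1. Reconcile the exclusion criteria, the discontinuation section and the monthly follow-up section, so that the protocol says explicitly whether the entry exclusions and an earlier safety withdrawal apply to primaquine in the monthly phase. The clinical rule is for the investigators to set; none is proposed here.
2. Make the reason for any withdrawal, and current pregnancy or breastfeeding status, available to staff at the monthly visit, for example as items on the monthly form.
3. In Table 2, mark adverse event assessment for M* and Mx, at least from any visit at which an antimalarial is given to the next visit.

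The cost is some wording, two table cells and a few more items at visits that already take place. No additional visits are needed.
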